## APPENDIX 17 – SYSTEMS USABILITY SCALE

| The System Usability Scale
Standard Version |                                                                                            | Strongly
Disagree  |                       |                       |                       | Strongly
Agree     |  |
|------------------------------------------------|--------------------------------------------------------------------------------------------|-----------------------|-----------------------|-----------------------|-----------------------|-----------------------|--|
|                                                |                                                                                            | 1                     | 2                     | 3                     | 4                     | 5                     |  |
| 1                                       | I think that I would like to use this system frequently.                                   |  |  |  |  |  |  |
| 2                                       | I found the system unnecessarily complex.                                                  |  |  |  |  |  |  |
| 3                                       | I thought the system was easy to use.                                                      |  |  |  |  |  |  |
| 4                                       | I think that I would need the support of a technical person to be able to use this system. |  |  |  |  |  |  |
| 5                                       | I found the various functions in this system were well integrated.                         |  |  |  |  |  |  |
| 6                                       | I thought there was too much inconsistency in this system.                                 |  |  |  |  |  |  |
| 7                                       | I would imagine that most people would learn to use this system very quickly.              |  |  |  |  |  |  |
| 8                                       | I found the system very awkward to use.                                                    |  |  |  |  |  |  |
| 9                                       | I felt very confident using the system.                                                    |  |  |  |  |  |  |
| 10                                      | I needed to learn a lot of things before I could get going with this system.               |  |  |  |  |  |  |

## APPENDIX 18 - App-based Visual Training Drills

The Senaptec App has a variety of drills to improve visuo-motor skills and can be run on any mobile device. As individuals improve, training adjusts automatically to remain challenging and promote continuous improvement. Examples of the type of training drills that will be used for this study are:

- **Eye Hand Coordination** - Find and touch the targets quickly and accurately.
- **Go / No-Go** - Touch the “Go” targets before they disappear, but do not touch the “No-Go” target. This requires quick decision making and swift movement.
- **Dynamic Vision** - Move your eyes to follow the target on the screen. This trains peripheral vision awareness and rapid eye movement.
- **Perception Training** - Symbols appear briefly, requiring the user to quickly see information in both central and peripheral vision. This can help the brain’s data collection and memory.
- **Response Inhibition** - Go targets and no-go targets appear momentarily in a single location. Touch the go target before it disappears and do not touch the no-go targets. This trains rapid decision making and muscle response.
- **Spatial Memory** - A set of targets will appear momentarily on the screen. You touch the screen in the locations the targets had appeared to work on memory skills.
- **Spatial Sequence** - A variation of spatial memory. In this module targets will appear and disappear sequentially. Touch the screen in the location and order the targets appeared.
- **Multiple Object Tracking** - The MOT skill often helps avoid collisions. Move a target to avoid collisions with multiple objects that are moving around the screen.
- **Depth Perception** - This module challenges and trains while the user stands at distance from the screen to make judgments of depth. Judging depth is fundamental for perceiving the world.
- **Near Far Shift** - This module uses the Senaptec handheld remote and a screen at distance to train the eye muscles to rapidly shift focus and recognize details. Quick near far shift capability is important in all areas of life, from sports to driving to walking through a store.
- **Visual Search** - Quickly find and touch the single target amongst the distractors. Search and find tasks are critical for navigating most sport and real-world activities.
- **Tempo** - Maintain rhythm by touching the target with each beat. This module is useful for training audio/visual correlation and anticipation timing.
- **Shape Cancellation** - Find and touch all the targets but do not touch the distractors. This training also serves as an assessment for visual neglect issues.
- **Visual Motor Integration** - Draw on the touch screen with your finger to repeat the pattern, either by tracing or looking at an adjacent shape. This training works on neuromotor skills.

Drills taken from: <https://www.senaptec.com/product/senaptec-app>

## Appendix 19 – Standard care (Active Control Interventions)

The active control interventions will include tasks, drills and modified games that are currently used in clinical practice. Below are some examples of the type of activities that participants will undertake during the active control phase of the study.

[figure not shown]

### Foundation drills

Vertical oculomotor stability

Pattern recognition

Attention to detail

[figure not shown]

### Perception drills

Block patterns (fixation, attention, problem-solving),

Visual memory (fixation, working memory)

Visual illusions

[figure not shown]

### Modified games

Hand-eye co-ordination (with visual challenges such as eye patch)

## Appendix 20 – Feasibility Outcomes

| Outcome              | Description                                                           | Analysis                                                                                                         |
|----------------------|-----------------------------------------------------------------------|------------------------------------------------------------------------------------------------------------------|
| Safety               | Adverse events (mild, moderate, or severe) caused by the intervention | Total number; compare differences in adverse events between the 2 arms.                                          |
| Amount               | Duration of actual visual training undertaken during each visit       | Compare average duration of visual training tolerated during each one hour visit [min]                           |
| Compliance/adherence | Rate of scheduled and completed sessions                              | Total n sessions completed /total n sessions scheduled (%)                                                       |
| Acceptability        | Motivation

Useability                                          | Pittsburg Rehabilitation Participation Scale Scores (compare mean scores between arms)
System Usability Scale |
| Equipment            | Function of mobile technology in participants' homes                  | Number of issues with equipment, such as break downs, shortage of equipment, internet access                     |

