### **Feasibility and Safety Analysis**

***Aim 1: Is a technological visual training intervention (using a combination of stroboscopic glasses and a tablet application) feasible, safe and acceptable for use in a Parkinson's population?***

Data will be presented as mean +/- standard deviation (normally distributed data) or median (interquartile range). Differences between the standard care and TVT group will be compared by two-tailed t-test (e.g. mean duration of visual training undertaken at each one hour visit), or chi-square test (e.g. total number of differences in adverse events between arms, compliance/adherence).

Feasibility outcomes will also be reported both descriptively and narratively in relation to usability and acceptability of the TVT package (see *Appendix 20*).

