### Mild Adverse Event

A mild adverse event is one that the symptoms are barely noticeable to the patient. It does not influence performance, require drug treatment or prevent the patient from carrying on with normal life activities.

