### Moderate Adverse Event

A moderate adverse event is one that the symptoms make the patient uncomfortable and causes some impairment to normal life activities. Treatment for symptom(s) may be required.

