### Severe Adverse Event

A severe event is one that the symptoms cause severe discomfort to the patient and the severity limits the patient's normal life activities. Treatment of symptom(s) may be required.

Ref. [Safety reporting - Health Research Authority \(hra.nhs.uk\)](https://www.hra.nhs.uk/safety-reporting/)

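### The only adverse event comparison named is an all-grade total of events, which can dilute an excess of moderate or severe harm in the TVT arm; report by grade and by participant beside it

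*Protocol*

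**What the plan says.** The Outcomes section ties feasibility to safety and acceptability and sends the reader to Appendix 20 for the full list. The Safety row there describes the outcome as "Adverse events (mild, moderate, or severe) caused by the intervention". Its analysis entry is "Total number; compare differences in adverse events between the 2 arms".

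The Feasibility and Safety Analysis section names the test: "chi-square test (e.g. total number of differences in adverse events between arms, compliance/adherence").

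Appendix 21 defines the grades:

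- Mild: "A mild adverse event is one that the symptoms are barely noticeable to the patient". Such an event does not affect performance and needs no drug treatment.
- Moderate: "A moderate adverse event is one that the symptoms make the patient uncomfortable and causes some impairment to normal life activities".
- Severe: "A severe event is one that the symptoms cause severe discomfort to the patient and the severity limits the patient's normal life activities".

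Serious events have a separate definition in Appendix 21. The Adverse Events section sends them to the University, and to the ethics committee if they are related and unexpected. No section tabulates or compares events by grade, or states how many participants had at least one event.

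**The concern.** The grade is part of the outcome's description but not of its stated analysis. In a plain total, a symptom that the participant barely notices counts the same as one that limits normal life. One participant with a recurring complaint over eight sessions also counts the same as several participants with one complaint each. If moderate or severe events cluster in the TVT arm while mild events are similar in both, the mild events add the same amount to each side and pull the ratio of totals towards 1.

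The serious-event route does not close this gap. It is a reporting duty, not a comparison by arm, and severe is not the same as serious. The effects that the protocol itself anticipates from strobe exposure or moving screens (headache, eye fatigue, nausea, cyber sickness) could be moderate or severe under Appendix 21 without meeting any of its seriousness criteria.

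What is at stake is how well the pilot answers the safety part of Aim 1, which feeds into whether a full-scale trial goes ahead.

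**Working it through.** **No figure to reproduce.** The protocol gives no adverse event rate and no safety-based sample size. The 40 participants (20 per arm) are justified as a pilot, without a power calculation. All event rates below are assumptions.

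**Set-up.** There are 20 participants per arm. Each has at most one moderate-or-severe event, with probability 0.30 (TVT) or 0.05 (control). Mild intervention-related events occur at the same rate λ per person in both arms. The totals are:

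- TVT: T = Poisson(20λ) + Binomial(20, 0.30), mean 20λ + 6.
- Control: C = Poisson(20λ) + Binomial(20, 0.05), mean 20λ + 1.

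The total fails to rank TVT as worse when T ≤ C, with probability Σₖ P(C = k) · P(T ≤ k). Summed exactly:

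| Mild events per person (λ) | Expected totals, TVT v control | Ratio | P(T ≤ C) |
|---|---|---|---|
| none (moderate-or-severe only) | 6 v 1 | 6.0 | 2% |
| 0.05 | 7 v 2 | 3.5 | 4% |
| 0.1 | 8 v 3 | 2.7 | 7% |
| 0.2 | 10 v 5 | 2.0 | 11% |
| 0.5 | 16 v 11 | 1.5 | 18% |
| 1 | 26 v 21 | 1.2 | 25% |
| 2 | 46 v 41 | 1.1 | 31% |

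The true excess is the same in every row, 5 moderate-or-severe events. Only the number of mild events changes.

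**Illustrative counts** (exact binomial test against a 50:50 split, treating events as independent):

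- TVT 8 mild + 7 moderate-or-severe, control 14 mild + 1: the totals are 15 v 15, p = 1.00. Moderate-or-severe alone is 7 v 1, p = 0.07.
- 20 mild in each arm, moderate-or-severe 8 v 1: the totals are 28 v 21, p = 0.39. Moderate-or-severe alone gives p = 0.04.

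**Participant level** (two-sided 5% test, 20 per arm, normal approximation). Let a share m of participants in each arm have a mild event, independently of the rest. The share with any event is then 1 − (1 − p)(1 − m), where p is the moderate-or-severe rate.

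| Moderate-or-severe, TVT v control | Alone | Any event, m = 20% | m = 40% | m = 60% |
|---|---|---|---|---|
| 30% v 5% | 0.55 | 0.26 | 0.15 | 0.10 |
| 40% v 5% | 0.78 | 0.44 | 0.26 | 0.16 |

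Example of an entry: for 30% v 5% and m = 20%, the shares with any event are 1 − 0.70 × 0.80 = 0.44 and 1 − 0.95 × 0.80 = 0.24.

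So pooling dilutes whether events or participants are counted. Counting participants deals with repeat events in one person, and only the split by grade deals with dilution by mild events.

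**The case against.** **Background symptoms.** A reader might infer that the total would mainly measure the ordinary complaints of people with Parkinson's. The documents do not support this. The Safety row limits the outcome to events caused by the intervention. The Adverse Events section records events whether related or not, but that is recording and not this outcome. Only intervention-related mild events can dilute the total, and their rate may be low: the Safety Considerations section calls soreness and fatigue after training a slight possibility. This is why the range above starts at 0.05 per person. The objection stands.

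**Grade thrown away.** A reader might also infer that the plan rules out showing grades. It does not. The row names them, Appendix 21 defines them, and the chi-square wording is given as an example. A by-grade table could also appear in an analysis plan that is not shown here. What remains is that the protocol states a specific analysis twice, and both times it is the total. An analysis plan that follows that wording need do no more.

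**Worst harms are visible anyway.** Serious events are escalated one by one, the supervising researcher keeps a running log, and 40 participants can be read case by case. This holds for serious events, but not for severe, non-serious ones compared by arm.

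**Little power either way.** True. Even 6 of 20 v 1 of 20 gives a Fisher exact p of 0.09, with exact 95% intervals of 12% to 54% and 0.1% to 25%. That argues for descriptive reporting, not for a total alone.

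**Conclusion.** The point holds in a limited form. The only adverse event comparison that the protocol names is a total of events between arms. It ignores grade and counts events, not participants, so it can dilute an excess of moderate or severe intervention-related harm.

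How much it dilutes cannot be derived from the documents. Under assumed moderate-or-severe rates of 30% v 5%, equal mild rates in both arms and 20 per arm, the total fails to rank TVT as worse with a probability of about 4% to 31%. The figure depends on whether mild events run at 0.05 or 2 per person; for moderate-or-severe events alone it is 2%. At the low end the loss is small. The protocol also attaches no decision rule to this ranking.

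A reader might go further and want moderate-or-severe events to replace the total as the safety result. The documents do not support that. This is a first study of the technology in this population, and low-grade headache, eye fatigue or nausea may itself be a tolerability signal, so the total and the mild events should stay in view. This is a cheap improvement to the reporting, not an error that invalidates the safety assessment.

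**What to change.** In the Safety row of Appendix 20 and in the Feasibility and Safety Analysis section, keep the all-grade total and add, for each arm:

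- the number of events by grade (mild, moderate, severe, and moderate-or-severe combined) and by seriousness;
- the number and proportion of participants with at least one event in each of those categories, with exact 95% confidence intervals;
- the risk difference between arms with its 95% confidence interval.

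State that these results are read descriptively and that no safety conclusion rests on a significance test at this sample size.

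The cost is a short change of wording in two places and one more table. The grades are already defined and named in the outcome, so no new data collection is needed.

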## **Appendix 21 – Safety Reporting Procedures for Adverse Events (Health Research Authority Guidance on Safety Reporting, Updated July 2020)**

An adverse event (AE) is any

- This includes events related to the intervention.
- This includes events related to the procedures involved (any procedure in the intervention).

Serious Adverse Events:

A Serious Adverse Event (SAE) is defined according to the health Research Authority (HRA) Guidance dated December 2010 as, any adverse event that:

- Results in death,
- Is life-threatening illness or injury, defined as an event in which the patient is at risk of death at the time of the event,
- Requires in-patient hospitalization or prolongation of existing in-patient hospitalization,
- Results in medical or surgical intervention to prevent life threatening illness or injury or permanent impairment to a body structure or a body function, or
- Results in persistent or significant disability\*/incapacity, or a permanent impairment of a body function or permanent damage to a body structure.

\*Disability is defined as a substantial disruption of a person's ability to conduct normal life functions.

*Severity of an Adverse Event*

### Mild Adverse Event

A mild adverse event is one that the symptoms are barely noticeable to the patient. It does not influence performance, require drug treatment or prevent the patient from carrying on with normal life activities.

### Moderate Adverse Event

A moderate adverse event is one that the symptoms make the patient uncomfortable and causes some impairment to normal life activities. Treatment for symptom(s) may be required.

### Severe Adverse Event

A severe event is one that the symptoms cause severe discomfort to the patient and the severity limits the patient's normal life activities. Treatment of symptom(s) may be required.

Ref. [Safety reporting - Health Research Authority \(hra.nhs.uk\)](https://www.hra.nhs.uk/safety-reporting/)
